**Figure 1 figure1:**
[figure not shown]
Study flow diagram.

### Recruitment

Participants will be recruited from across the United States via advertisements placed on social media platforms (eg, Facebook, Instagram, and advocacy groups/sites aimed specifically at TY, such as Transgender Alliance and Affirming Transgender Rights; see Figure 2). Online dating apps with transgender users (ie, Scruff) will also be used. Advertisements will include depictions of young people from a variety of racial and ethnic groups to encourage inclusivity and the participation of TY from a variety of backgrounds. Information about the study will also be shared via transgender media personalities’ social media accounts.

When a potential participant clicks on an advertisement, they will be taken to a page containing basic study information, including a short description of study activities. If the individual expresses interest in participating in the study, they will be directed to the study consent form. For participants aged 15-17 years, consent will only be obtained from the participant acting as an emancipated minor. Due to the sensitive nature of the study topic and the stigma and discrimination TY may face from their parents or guardians, requiring parental consent may endanger the safety and wellbeing of the participant. Waiving parental consent allows those who have not fully disclosed their gender identity, or whose guardians are not accepting, to participate in the study.

### Study Procedure

After providing consent electronically, participants will be directed to a short eligibility screener. If eligible, a potential participant will register for the study by providing their contact information. This information includes an email address, mobile phone number, physical mailing address, and preferred choice of name and pronouns. It is important to note that many TY have unstable housing or may not feel comfortable having mail, however discreet, sent to their home address. For this reason, the registration form will ask for a physical address to which the participant feels safe and comfortable receiving mail. As soon as the consent form, screening questionnaire, and site registration are complete, the participant will receive an email with instructions on completing the baseline survey. After completing the baseline survey, each participant will be randomized to either the control arm (HIV self-testing only) or intervention arm (video-based counseling in conjunction with HIV self-testing), using a 1:1 treatment allocation. The treatment assignments will be generated with the use of a pseudo-random number generator, which uses permutated blocks to ensure balance in the number of participants assigned to each arm. The randomization process will generate one of two emails to study participants, indicating whether they will be receiving HIV self-testing or video-based counseling plus HIV self-testing.

**Figure 2 figure2:**
[figure not shown]
Sample online advertisement.

#### Control Arm

TY in the control arm will receive one home-based HIV self-testing kit delivered in discreet packaging. In addition to an oral fluid test kit (OraQuick), the package will contain condoms, water-based lubricant packets, and one pair of ear buds. All OraQuick tests will be assigned a specific identification (ID) number that will link to the participant’s study ID number. Upon taking the test, participants will be directed to enter their results on the study website. For those who report a positive result, a message will automatically be sent to the study coordinator. Study staff will then call the participant to offer information regarding places where the participant may acquire a confirmatory HIV test, as well as HIV care services and counseling in their local area or another area of their choosing.

#### Intervention Arm

The intervention arm is a combination of HIV self-testing and HIV test counseling offered remotely via a HIPAA-compliant video-chat session. Participants in the intervention arm also receive one OraQuick test, condoms, lubricant, and earbuds via mail, but will be informed to leave their package *unopened* until directed by the counselor during the video-chat session. Participants will be instructed via email on how to download the VSee software prior to the video-chat session. VSee is available as downloadable software for Windows and Macintosh and as an app in the iOS and Android marketplaces [27]. This software allows participants to log into the video-chat from a desktop, laptop, tablet, or smartphone. Both the software and app versions of VSee contain voice, video, and screen-sharing capabilities to provide a fully-functional counseling session across platforms and devices. VSee provides high-quality video at speeds as low as 50 kilobits per second, allowing full functionality in areas without access to broadband or high-speed cellular data networks [27]. The one-time counseling session lasts approximately 30-45 minutes and consists of two consecutive phases.

Phase one of the counseling session will use elements of motivational interviewing to ascertain reasons (eg, structural, lack of information/misinformation on HIV testing) why the participant has not tested for HIV in the past 12 months. The counselors will also ask about some of the participant’s recent sexual behaviors (eg, number of partners, use of condoms, sexual activities) to establish those that may pose a risk for acquiring HIV. The answers to these questions will form the basis for phase two. Counselors will attempt to provide solutions to mitigate each of the participant’s concerns regarding HIV testing. For structural concerns such as lack of transportation or cost of testing, the counselor might talk about locating local HIV testing services, retailers that sell HIV self-testing kits, and options for free HIV testing in their local area. If the participant reports not testing due to a lack of knowledge of where to test or fear of being recognized at local testing sites, the counselor will assist the participant in finding testing options in nonlocal gender-affirming spaces, and help establish a transportation plan. For participants who report a lack of information or misinformation on the need for HIV testing, the counselor will talk through risk factors for HIV transmission and the CDC recommendations for testing specific to TY. The screen-sharing function in VSee will allow the counselor to share online resources and instruct the participant on their use (eg, how to navigate AIDSVu.com or local health department websites). For those who report fear of stigma or discrimination, the counselor will provide advice on their rights as a patient, including their right to confidentiality, respect, and privacy. The counselor may also share the Gay and Lesbian Medical Association resource list with the participant, which includes *10 Things Transgender Persons Should Discuss with their Health Care Providers* [28]. Through role playing with the counselor, the participant will practice talking about sex and HIV with a health care provider. The counselor will help the participant formulate and practice specific talking points to use with their provider. The counseling will place emphasis on providing the participant with the skills necessary to routinely test for HIV by addressing individual barriers to testing, and giving each participant a supportive and affirming HIV testing experience.

Phase two of the session will consist of testing for HIV. Prior to the test, counselors will offer standard content for risk elicitation and identification of safer sex goal behaviors. The participant, directed by the counselor, will conduct their own test and read their own results. They will then show the counselor their test result for confirmation. Based on the results of the test and the information gathered in phase one, the counselor will assist the participant in developing a prevention or care plan to reduce the risk of acquiring or transmitting HIV (eg, number of sexual partners, frequency of unprotected intercourse). The counselor will describe the behavioral and biomedical interventions appropriate for each participant, such as condom use, partner reduction, decreasing drug or alcohol use, and/or preexposure prophylaxis (PrEP). At the end of the video-chat session, participants who show a positive result will be counseled on the need for timely confirmatory testing and linkage to care. The counselor will arrange a time within one week of the initial session to conduct a second video-chat session. During the second session, the counselor will determine other resources from which the participant may benefit, such as medical case management, mental health care, and/or more comprehensive psychological counseling and services. TY who test positive will also be directly linked to medical care in the second session by connecting them with a provider in their local area or another area designated by the participant. Study staff will follow up on the next business day to ensure that contact was made with the participant’s desired facility. The participant will be contacted at least three more times: (1) to confirm an appointment was scheduled, (2) to confirm that the appointment was attended, and (3) to report confirmatory test results.

#### Counselor Training

Counselors will be trained to use motivational interviewing during a two-day training session. The training will involve didactic presentations on the history, science, and spirit of motivational interviewing, as well as role plays with other counselors acting as study participants. The counseling session protocol was developed with the input of transgender-identified staff members and community members. All counselors will be trained in HIV testing and counseling, and receive specific training on the importance of gender affirmation and working with TY prior to delivering the intervention. Counselors who demonstrate proficiency via audiotaped role plays reviewed by study staff will be cleared to deliver remote counseling to participants. To examine protocol fidelity, all sessions will be audio-taped and research assistants will code and assess a random sample of sessions each month using the *Motivational Interviewing Treatment Integrity* (MITI-4) coding scheme [29-32], and qualitatively assess empathy and motivational interviewing-adherent and nonadherent behaviors. Counselors identified as having treatment drift will receive booster trainings as necessary.

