#### HIV Testing

Analyses will be conducted using logistic regression. The proportion of participants who obtain at least one HIV test within the follow-up period will be calculated for each study arm, along with corresponding 95% confidence intervals. First, the regression model will be fit using study arm only. A second model will control for baseline characteristics, as well as self-reported stigma and discrimination to measure their roles in mediating the outcome.

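### The primary logistic model treats participants as independent although one arm is grouped by counsellor; a partially nested sensitivity analysis, and a fidelity draw spread across counsellors, would cover this cheaply

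*Protocol article*

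**What the plan says.** **Analysis.** In the protocol article, Statistical Analysis, HIV Testing, the primary outcome (at least one HIV test during follow-up) is analysed by logistic regression: "First, the regression model will be fit using study arm only". Then: "A second model will control for baseline characteristics, as well as self-reported stigma and discrimination". The proportions testing "will be calculated for each study arm, along with corresponding 95% confidence intervals". Counsellor appears in neither model. It is also absent from the Poisson GEE for sexual risk-taking, which is there for repeated three-month counts, and from the logistic model for linkage to care.

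**Delivery.** Under Intervention Arm, "The one-time counseling session lasts approximately 30-45 minutes". It is tailored to each participant's own barriers to testing. Control participants test alone and report on the website. The article speaks of counsellors in the plural but does not say how many there are or how participants are assigned to them.

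**Fidelity.** Under Counselor Training, "Counselors who demonstrate proficiency via audiotaped role plays reviewed by study staff will be cleared to deliver remote counseling to participants". After that, every session is taped and "research assistants will code and assess a random sample of sessions each month", using the MITI-4 scheme. The consequence falls on the individual: "Counselors identified as having treatment drift will receive booster trainings as necessary".

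**The concern.** Participants who see the same counsellor share that person's skill, style and any drift. The session is meant to change later testing, which is the primary outcome, so testing rates may differ between counsellors. The protocol's own provision for drift accepts that delivery can vary in this way. The grouping exists in one arm only (a partially nested design). A model that assumes independence leaves out the between-counsellor part of the intervention arm's variance. If that part is above zero, the confidence interval for the arm effect is too short and the test rejects too often. The estimated arm effect itself is little affected.

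The fidelity point is smaller. Sessions are sampled but counsellors are retrained, so a draw that does not ensure coverage of each counsellor may be slow to show that one of them has drifted.

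**Working it through.** **Inputs from the protocol article**
- 200 completers with 1:1 allocation, so 100 per arm. The enrolment target reproduces: 200 / (1 − 0.20) = 250 (Sample Size).
- The stated models have no counsellor term (Statistical Analysis, HIV Testing).
- The article gives no figure for clustering that could be reproduced.

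**Assumed inputs (not in the article)**
- Number of counsellors k = 3 to 8, with equal caseloads m = 100/k.
- Intraclass correlation (ICC) 0, 0.02 or 0.05.
- Every intervention participant attends a session.
- Outcome variance is similar in the two arms; nominal two-sided alpha is 0.05.

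**Formulas**
- Design effect in the intervention arm: DE = 1 + (100/k − 1) × ICC. In the control arm DE = 1.
- The intervention-arm standard error (SE) rises by √DE.
- The SE of the difference rises by √((1 + DE)/2).
- Actual alpha = 2 × (1 − Φ(1.96 / that factor)).

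**Numbers put in**
- k = 3, ICC 0.02: DE = 1 + 32.33 × 0.02 = 1.65; √(2.65/2) = 1.150.
- k = 8, ICC 0.02: DE = 1 + 11.5 × 0.02 = 1.23; √(2.23/2) = 1.056.
- k = 3, ICC 0.05: DE = 1 + 32.33 × 0.05 = 2.62; √(2.62/2 + 0.5) = 1.345.
- k = 8, ICC 0.05: DE = 1 + 11.5 × 0.05 = 1.575; √(2.575/2) = 1.135.

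| k | ICC | DE | Intervention-arm SE × | SE of difference × | Actual alpha |
|---|---|---|---|---|---|
| any | 0 | 1.00 | 1.00 | 1.000 | 0.050 |
| 3 | 0.02 | 1.65 | 1.28 | 1.150 | 0.088 |
| 8 | 0.02 | 1.23 | 1.11 | 1.056 | 0.063 |
| 3 | 0.05 | 2.62 | 1.62 | 1.345 | 0.145 |
| 8 | 0.05 | 1.58 | 1.25 | 1.135 | 0.084 |

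Participants who never attend belong to no counsellor's group, so non-attendance lowers these factors. Unequal caseloads would raise them.

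**Fidelity draw, for illustration.** Suppose 20 sessions in a month, four counsellors with five sessions each, and a simple random draw of three recordings (all assumed). The chance that a given counsellor is not drawn that month is C(15,3)/C(20,3) = 455/1140 = 0.40. With five recordings it is C(15,5)/C(20,5) = 3003/15504 = 0.19.

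**The case against.** **On the analysis.** The size rests wholly on assumed inputs. Contact is one short session, while the outcome is self-reported testing over six months, so the correlation may be small. With 10 counsellors and an ICC of 0.01, the SE of the difference rises by only 2%. A sensitivity analysis is also something that an article can leave to a statistical analysis plan, and that plan is not shown. All of this stands. A reader might infer that the published intervals will be too narrow; the article does not support that as a fact, because it gives neither the number of counsellors nor an ICC. What remains is that the models the article does set out assume independence, while delivery in one arm is grouped.

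**On fidelity.** A reader might infer that the sample ignores counsellor. The text does not say so: a random sample can be stratified, and the sampling fraction and strata may be in the full protocol. Counsellors are cleared individually, every session is taped and coding repeats monthly. Nor does it follow that drift goes uncorrected. If 20% of sessions were coded (an assumption), a counsellor with three sessions a month would escape review in a single month with probability 0.8³ = 0.51, over three months 0.8⁹ = 0.13, and over six months 0.8¹⁸ = 0.02. The risk is late detection. A rule of one recording per counsellor every month could also exceed the planned total. Results reports 12 sessions from June 19 to August 21, 2017, about six a month, although this is a start-up count; 3 to 8 counsellors would then need 3 to 8 recordings. That is why the fix holds the total fixed.

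**Conclusion.** The point holds conditionally and at low severity. The stated primary models leave out counsellor in a partially nested design. If the within-counsellor correlation is above zero, the interval for the arm effect is too short. For 100 intervention participants and 3 to 8 counsellors, the true standard error of the difference would be 5.6% to 15.0% larger than reported at an ICC of 0.02, and 13.5% to 34.5% larger at 0.05. There is no effect at zero, and a smaller one if some participants never attend. Counsellor number, ICC, equal caseloads and full attendance are assumptions.

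The fidelity point is secondary: the article gives no assurance that each counsellor is reviewed at regular intervals, but it does not rule this out.

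**What to change.** **Statistical Analysis, HIV Testing.** Keep the arm-only logistic model as primary. State the number of counsellors and carry a counsellor identifier into the analysis data; the fidelity procedure already implies a link from session to counsellor. Add a sensitivity analysis with a counsellor effect in the intervention arm only, each control participant forming their own cluster, and a small-cluster correction. Report testing rates by counsellor descriptively, since the article does not say that participants are randomised to counsellors.

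**Counselor Training.** Draw the same total number of recordings, stratified by counsellor or rotating across counsellors, so that each is reviewed at regular intervals.

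**Cost.** One further model, one variable and a different draw of the same number of tapes. The downside is a slightly wider interval that is imprecisely estimated with few counsellors, which is why it belongs in a sensitivity analysis. For a pilot, the variation between counsellors is also useful in planning a larger trial.

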### Measures

Measures will be collected via the baseline, three-month, and six-month online surveys. All measures included in the baseline and follow-up questionnaires were included after a review of the current literature on TY.

#### Outcomes

The primary outcome for this study is routine HIV testing, defined as testing at least once during the follow-up period (ie, every 3-6 months) based on the HIV risk profile of the participant. Secondary outcomes consist of sexual risk-taking behaviors, intervention acceptability at the final survey, and linkage to HIV care (for those who report a positive result at baseline or during the course of the intervention). Key covariates include measures of transphobia and social marginalization.

#### Demographics and HIV Knowledge and Testing History

The demographics section includes measures of age, education, race, ethnicity, sexual orientation, employment, and state of residence. Both the respondent’s sex assigned at birth and current gender identity will be collected. Previous literature on the sexual health of transgender individuals has been criticized for not using discrete categories for trans-masculine/transmale and trans-feminine/transfemale [33]. For this reason, current gender identity will include options for male, female, trans-masculine/male, trans-feminine/female, as well as categories for genderqueer/gender nonconforming, agender/genderfluid individuals, and a participant-driven response option. Items used in previous studies of LGBT persons will measure knowledge regarding the transmission and prevention of HIV [33,34], and knowledge and use of PrEP [34], at baseline and at each follow-up point.

#### HIV Testing

History of HIV testing, including measures of frequency, place of testing, method of testing, and linkage to care (if HIV-positive), will also be collected at baseline. Follow-up surveys will repeat the questions from the baseline and will also ask questions regarding HIV testing since the last survey. These parameters include location of test (eg, home, Acquired Immunodeficiency Syndrome Service Organization, Department of Public Health, or physician), test result, care received (specifically for HIV-positive participants), and reason for testing (ie, routine care versus episodic exposure).

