Another important limitation of the current telehealth literature concerns its use as an information dissemination and case management tool. Few studies use this technology for actual clinical care, such as HIV testing. With approval by the US Food and Drug Administration in 2011, high quality (sensitivity 93.64%, 95% CI 82.46-98.66; specificity 99.87%, 95% CI 99.28-100.00 [20]), home-based HIV testing is now available commercially in all 50 states [21]. However, critiques of home-based HIV testing include difficulty interpreting the results, a lack of posttest counseling for the adoption of safer HIV prevention methods, and a lack of proper linkage to care [22]. Adding online counseling through video-chat software to home-based HIV testing has the potential to mitigate these concerns. Through telehealth-delivered counseling, individuals can receive tailored, convenient, and confidential support that due to stigma, discrimination, and/or lack of locally-available services, may not otherwise be received. While there are few telehealth-based HIV prevention interventions published in the literature, results from prior studies show increased knowledge, self-efficacy, and motivation towards effective HIV prevention methods [23-26].

This paper describes the protocol for the first study to combine telehealth and home-based HIV testing for comprehensive, gender-affirming HIV testing and counseling for TY. In this study, approximately 200 TY aged 15-24 years will be randomized into either a control group that receives an HIV self-testing kit or an intervention group that receives an HIV self-testing kit as well as a video-chat counseling session provided by a trained HIV counselor. The main outcome of this study is the frequency of HIV testing in the six months following initial testing. The study aims to examine whether the receipt of an HIV self-testing kit plus a video-chat-delivered counseling session can create changes in HIV testing behavior, sexual risk-behaviors, and linkage to care for newly-diagnosed HIV-positive TY. If successful, this low-cost intervention has the potential to shape the delivery of HIV prevention and care services to this population, who are currently overlooked in HIV programming, research, and prevention efforts.

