## Methods

### Study Overview

This study is a pilot randomized controlled trial (RCT) of 200 self-identified TY aged 15-24 years, recruited via a range of social media platforms. Participants will be randomized to one of two study arms. TY in the control arm will receive one HIV self-testing kit by mail and will be asked to report their results via a study website. TY in the experimental arm will also receive one HIV self-testing kit via mail, and will conduct this test under the supervision of a remotely-located counselor during a prescheduled video-chat session. Participants in both arms will complete a baseline survey upon recruitment, with repeat surveys at three and six months posttesting (see Figure 1). Participants will receive email and SMS reminders to log into the study website to complete follow-up surveys. The primary outcome for this study is routine HIV testing during the follow-up period. Secondary outcomes include sexual risk-taking behaviors, intervention acceptability, and linkage to care for those who test positive for HIV.

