### Statistical Analysis

The primary outcome will be the proportion of TY who tested for HIV at least once in the six-month follow-up period. Descriptive statistics of participant characteristics will be presented for all participants and also by study arm. These results will be compared using student t-tests or Wilcoxon rank sum tests for continuous variables, and Chi-square tests for categorical variables. The analysis for each outcome measure is described in detail below.

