## Results

Project Moxie began recruitment on June 19, 2017 and has enrolled 130 participants as of August 21, 2017. Self-testing kits have been mailed to a total of 71 participants. Video-chat sessions for 12 participants randomized to the experimental arm have been completed and 58 participants from the control arm have entered their test results into the study database.

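### The month-3 recall window reaches back before the study kit is used and the primary outcome does not exclude that kit, so the study's own test can be counted as the outcome

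*Protocol article*

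**What the plan says.** **Order of events.** Study Procedure states: "After completing the baseline survey, each participant will be randomized to either the control arm" or to the intervention arm. The kit is used after that. Control participants test on their own and enter the result on the study website (Control Arm). Intervention participants keep the package closed until the counselor directs them during the video session (Intervention Arm).

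**Recall window.** Under Measures, HIV Testing: "Follow-up surveys will repeat the questions from the baseline and will also ask questions regarding HIV testing since the last survey". For tests since the last survey, the items named are location (home is one example), result, care received and reason. The repeated baseline items add frequency, place and method. Neither a test date nor the source of a kit is named.

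**Outcome.** The Outcomes section has routine testing "defined as testing at least once during the follow-up period (ie, every 3-6 months) based on the HIV risk profile of the participant". Statistical Analysis has: "The primary outcome will be the proportion of TY who tested for HIV at least once in the six-month follow-up period". Neither says whether the study kit counts.

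**Intended window.** The Introduction says: "The main outcome of this study is the frequency of HIV testing in the six months following initial testing". Study Overview says: "Participants in both arms will complete a baseline survey upon recruitment, with repeat surveys at three and six months posttesting".

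**The concern.** The article describes two different windows. The Introduction and Study Overview start the clock at the study-kit test. The month-3 survey starts it at the baseline survey, which comes earlier. A participant who answers the month-3 question truthfully will report the study kit, and a rule that one test is enough then scores that participant as a success.

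The trial asks whether counseling leads to further testing. If the supplied test satisfies the outcome, nearly every kit user succeeds whatever they do afterwards. The arm comparison then mostly reflects who used the mailed kit.

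**Working it through.** **1. The windows side by side**

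- Survey at month 3: from baseline survey to month 3. Contains the study-kit test.
- Survey at month 6: from the month-3 survey onward. Does not contain a kit used before month 3.
- Introduction: six months starting after the initial test. Does not contain the study-kit test.

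The conflict therefore sits in the month-3 item, but one positive answer there is enough to meet the outcome.

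**2. Whether the named items separate the two kinds of test**

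A study kit used at home and a self-bought kit used at home give the same location and method. Dropping all home tests would not solve this, because counselors may tell participants about shops that sell self-test kits (Intervention Arm, phase one). A later purchased test can be a real intervention effect. A reported count helps only if it is known whether the respondent included the study kit.

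**3. Model**

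The article gives neither kit use nor the later testing rate, so both are assumptions here. Let k be the share using the study kit and q the share testing again afterwards, taken as independent. If the kit counts:

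observed rate = 1 − (1 − k)(1 − q)

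**4. Equal kit use in both arms**

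observed difference = (1 − k)(q_int − q_ctrl)

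- k = 80%: 0.20 × 10 points = 2 points
- k = 90%: 0.10 × 10 points = 1 point

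Sample Size plans for differences of 10, 12 and 15 points.

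Power is taken at 100 per arm (200 completers, 1:1) with two-sided alpha 0.05 (assumed), by the normal approximation with pooled variance under the null, counting only the tail in the true direction. The article's own 81%, 92% and 99% are not reproduced at 100 per arm under any control rate tried; the closest two-sided fit, a control rate of 1.4%, gives 82.9%, 90.6% and 96.6%. That is a separate matter and does not affect this point. For a true 30% versus 40%:

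- kit excluded: 31.6%
- kit counted, k = 80% (86% versus 88%): 6.2%
- kit counted, k = 90% (93% versus 94%): 4.7%

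Over control rates from 50% down to 2%, power for a true 10 points is 29% to 80% with the kit excluded and about 4% to 7% with it counted.

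Independence is not a harsh assumption. Once the kit counts, only participants who did not use it can contribute to a difference. In the intervention arm these will mostly be people who did not complete the counseling session.

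**5. Unequal kit use, no true effect, q = 30% in both arms**

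- Control 90%: 1 − 0.10 × 0.70 = 93%
- Intervention 70%: 1 − 0.30 × 0.70 = 79%, difference −14 points
- Intervention 80%: 1 − 0.20 × 0.70 = 86%, difference −7 points
- Reversed (control 80%, intervention 90%): 86% versus 93%, difference +7 points

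**6. The snapshot in Results**

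The article reports 130 enrolled, 71 kits mailed, 12 intervention sessions completed, and that "58 participants from the control arm have entered their test results". If each of the 58 control results came from a mailed kit, at most 71 − 58 = 13 kits had gone to the intervention arm, and 12 sessions were complete. On the same assumption for the sessions, 58 + 12 = 70 of 71 mailed kits had been used. This suggests high use once a kit is mailed. It does not show a difference in use between arms.

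**The case against.** No passage says that the study kit counts, and several point the other way. The Introduction sets the outcome after the initial test, follow-up surveys are timed from testing, and Outcomes speaks of a positive result at baseline, which treats the kit test as the starting point. The article only summarizes the questionnaire, so its list of items need not be complete. Kit use is also recorded elsewhere: kit IDs link to study IDs, control results go to the website, and intervention participants show their result to the counselor. The data to remove the kit test therefore largely exist.

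Most of this stands, and it limits the point to a risk created by the stated recall window and the open outcome definition. It does not remove the risk. The intent in the Introduction does not take a test out of the survey answers, and no stated rule uses the kit or session records to define the outcome.

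A reader might infer more: that the plan defines kit use as success, and that the comparison will reverse because control kit use is far higher. The documents support neither. The 58 versus 12 becomes 89% versus 18% only by assuming 65 randomized per arm and ignoring that just 71 kits had been mailed. The gap may simply be a lag in mailing or scheduling. Lower final uptake in the intervention arm is plausible, since a session must be booked, but nothing establishes it, and higher uptake there would inflate the effect instead.

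**Conclusion.** The point holds as a conflict to be reconciled. The month-3 recall window takes in the study-kit test, the outcome definitions do not exclude it, and the Introduction and Study Overview intend a window that begins after it. As described, the study-kit test can be counted as the primary outcome.

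The size depends on the kit being counted and on assumed uptake. With high and similar use, most of the true difference disappears: 80% to 90% use removes 80% to 90% of it. With unequal use, the bias can favor either arm, at 7 to 14 points in the examples above. The direction in this trial is unknown. Because the primary comparison is at stake and the correction is cheap, it should be settled before the month-3 data are analyzed.

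**What to change.** - Define the primary outcome as at least one HIV test other than the study-supplied kit, in a six-month window that starts after the study-kit test. Use the same wording in Introduction, Outcomes and Statistical Analysis.
- For participants who never use the kit, set a fixed index date, such as a set interval after randomization or kit mailing, so that they stay in the analysis.
- Word the month-3 item to exclude the mailed kit, or collect the date and source of each reported test.
- Before analysis, reconcile reported tests with the ID-linked kit results and the session records, including for any month-3 surveys already completed under the present wording.

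The cost is a small survey and ethics amendment and a data-cleaning rule. Recruitment began on June 19, 2017 and the first follow-up survey comes three months after testing, so none was due by the article's August 21, 2017 status date.
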